# Effect of probiotics on nasal and intestinal microbiota in people with high exposure to particulate matter ≤ 2.5 μm (PM2.5): a randomized, double-blind, placebo-controlled clinical study

**DOI:** 10.1186/s13063-020-04759-4

**Published:** 2020-10-14

**Keywords:** Air pollution, Ambient particulate matter, Respiratory system, Microbiota, Probiotic, Randomized controlled trial

## Abstract

**Background:**

Extended exposure to high concentrations of PM2.5 changes the human microbiota profile, which in turn may increase morbidity and mortality due to respiratory system damage. A balanced microecosystem is crucial to human health, and certain health-related problems may be addressed by effective microecosystem regulation. Recent studies have confirmed that probiotics may reduce the incidence of respiratory diseases. However, few studies have investigated probiotic treatment outcomes in subjects exposed to high concentrations of PM2.5.

**Methods:**

This study is designed as a prospective, randomized, participants- and assessor-blinded, placebo-controlled trial. One hundred and twenty eligible volunteers recruited from October 2019 to July 2020 in downtown Chengdu, China, will be treated with either probiotics or placebo over 4 consecutive weeks. The primary outcome will be 16SrRNA sequencing assay data from nasal and intestinal secretions. Secondary outcomes will be pulmonary function, score on a gastrointestinal symptom rating scale, COOP/WONCA charts, and the Short-Form Health Survey 36 for quality of life. Results will be analyzed to assess differences in clinical efficacy between groups. Six-month follow-up examinations will evaluate the long-term value of probiotics on cardiovascular and respiratory disease end-point events.

**Discussion:**

We will explore the characteristics of nasal and intestinal microbiota in a population with high exposure to PM2.5. Probiotics and placebo interventions will be tested for efficacy in microbial balance regulation, effects on lung and physical functions, and quality of life improvement. This study is expected to provide reliable evidence to support the widespread promotion of probiotics in clinical practice for the protection of individuals with high exposure to PM2.5.

**Trial registration:**

Chinese Clinical Trial Registry ChiCTR1900025469. Registered on 27 August 2019.

## Background and rationale

Due to the rapid development of industrialization and urbanization in China, air pollution has become one of the main risk factors for diseases among Chinese citizens [1]. In particular, the recent and frequently occurring hazy weather caused by PM2.5 has seriously affected the health and quality of life of the population [2, 3]. PM (fine particulate matter) is the general name for solid and liquid particles suspended in ambient air [2, 4]. Particle size is the most important factor in air pollution, and PM2.5 is a fine particle with a size of ≤ 2.5 μm. PM2.5 may adsorb a variety of organic compounds, heavy metals, pathogenic microorganisms, and acid oxides and may enter the lower respiratory tract during respiratory movement, reaching the alveoli and possibly the blood circulation. These characteristics implicate PM2.5 as a potential cause of the recent increase in respiratory disease incidence [5]. Numerous epidemiological studies have revealed that long-term exposure to PM2.5 pose great risks to human health. Such as, the increase of PM2.5 concentration is closely correlated to the hospitalization rate and mortality associated with respiratory diseases [6–9]. Long-term exposure to PM2.5 can lead to an increase in emphysema [10] and small airway resistance [11]. The meta-analysis of global association of air pollution and heart failure indicated that air pollution especially the high concentration of PM2.5 has a close temporal association with heart failure hospitalization and heart failure mortality [12]. The studies also suggest that air pollution is one of the residual risk factors of CAD, and long-term exposure to fine particulate air pollution is associated with degree of coronary artery calcification, ischemic heart disease, and stroke mortality [13–15]. Another study shows that exposure to traffic air pollution may contribute to acute changes in blood pressure and autonomic and micro-vascular function in women [16]. High concentrations of environmental particles carry a large number of microorganisms, including many pathogens and opportunistic pathogens [17, 18]. Particulate matter is one of the key factors affecting the airborne bacterial concentration and community structure [19, 20]. Several studies demonstrated that high-levels of PM2.5/PM10 were related to alterations in the human pharyngeal [21], nasal [22], and intestinal [23] microbiota composition. Long-term exposure to PM2.5 as the main component in air pollution disrupts the inherent balance of the human microbiota and may induce and aggravate respiratory diseases. The nasal cavity as an independent official orifice, the nasal mucosa is not easily disturbed by diet, drugs, and other external factors, so the resident microbiota in the nasal cavity is also one of the typical characteristics of our body; it plays an important role in the maintenance of human health and the occurrence of diseases. Studies have confirmed the importance of nasal pathogens in lung diseases [24, 25]. It has been reported that exposure to environmental fine particles can also change the structure of nasal [26] and intestinal microbiota [27], so we choose nasal and intestinal microbiota as evaluation indicators.

The Food and Agriculture Organization of United Nations/World Health Organization (FAO/WHO) Expert Committee has defined probiotic strains as “live microorganisms which, when consumed in appropriate amounts in food, confer a health benefit on the host” [28]. The main probiotic component selected for this clinical trial is *Lactobacillus rhamnosus* GG (LGG). Studies confirmed that LGG may regulate the human microbiota, positively affects immunity, has anti-inflammatory properties, and produces a biofilm that can mechanically protect the mucosa [29]. However, few studies have investigated these positive effects on individuals exposed to high concentrations of PM2.5. A randomized, double-blind controlled clinical trial will be conducted in this study to investigate the characteristics of nasal and intestinal microbiota and the preventive and therapeutic effects of probiotics in healthy subjects exposed to an environment containing PM2.5. We hope to provide a clinical basis for the prevention and treatment of respiratory and circulatory diseases based on the study results.

## Methods

### Study design

This study incorporates a randomized, double-blind, placebo-controlled clinical trial and was developed according to the Standard Protocol Items: Recommendations for Interventional Trials (SPIRIT) Statement (the SPIRIT checklist is shown in Additional file 1). The nasal and intestinal secretions of subjects exposed to PM2.5 will be collected and analyzed to determine the characteristics of nasal cavity and intestinal flora under high PM2.5 exposure and to investigate the clinical efficacy of probiotic intervention. A flowchart of this trial procedure is shown in Fig. 1. The Chinese Ethics Committee of Registering Clinical Trials (Ethical Review No.: ChiECRCT20190173) approved all the methods and ethics in the present study, and all procedures are in accordance with the Declaration of Helsinki v.08. Participants will sign a written informed consent form (see Additional file 2) with a clear understanding of the purpose, study procedure, and all potential risks related to the trial. All written informed consent forms will be collected and provided to members of the experimental group.

**Fig. 1 Fig1:**
[figure not shown]
Study process: flowchart of study procedure

### Participant recruitment

We will recruit 120 candidates. The recruitment methods used in this study include (1) face-to-face communication, (2) bulletin boards, and (3) posters. We will post this recruitment information in neighborhoods and subdistrict offices based on the high concentration of PM2.5 published by the Environmental Supervision Administration, and the recruitment information will also be posted on the bulletin boards of the Environmental Protection Agency and the Transportation Administration. Members of the research group ([name], [name], [name], [name], [name]) will be responsible for recruiting participants, all of whom are medical staff who have obtained physician certificates. After the start of the project, these members will receive the training of this project and take our project notice to communicate with the participants about the project. These trained members of the research group will obtain the written consent of the participants. Any eligible participant can contact our researchers using the provided telephone number and undergo screening to enter the group. Only those who fully meet the selection criteria, and sign the written informed consent form, will be registered and randomly assigned to placebo or probiotic treatment. All participants will be required to undergo a routine physical examination and complete the relevant questionnaire. There is no anticipated harm and compensation for trial participation. All subject personal information and data will be considered confidential. Only the members of our research group and the principal investigator will have access to the database. After the late data entry is completed, participants can log on to the website (http://www.medresman.org.cn/login.aspx) to query the details. The datasets analyzed during the current study are available from the corresponding author on reasonable request. Participant enrolment will begin in October 2019 and end in July 2020.

### Sample size

Sample size calculation was performed with G*Power 3.1 [30], using *F* test between factors with two groups (intervention and placebo) and three evaluation sessions (before administration, after administration, 12 and 24 weeks after administration). Since there was no pre-experiment before, we chose to take the average effect as 0.25, an *α* error probability of 0.05, and a power (1-β error probability) of 0.80. We take the Corr among rep measures as 0; the Nonsphericition correction ɛ is 1/(4–1) ≈ 1.34; the resulting total sample size is 95, because it has to be repeated 4 times; and the final sample size of each group is 24. Allowing for a maximum dropout rate of 30%, the number of subjects in the treatment group has been set to 30 participants. Based on the needs of our project, it is proposed to recruit high PM2.5 exposure and low PM2.5 exposure groups, and the groups are divided into intervention and placebo groups, according to each group requires a sample size of 30 patients, for a total of 120 patients.

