### Statistical methods

Analysis will be performed using BMISPSSStatistics24.0 software. Results will be considered statistically significant if *p* ≤ 0.05. Since the data should compare changes within groups, between groups and between-groups, and in order to reduce the probability of errors, two-way analysis of variance of repeated measurements will be used to explore the impact of time and time-group effects, and Bonferroni post-test will be used to adjust. Analysis of variance (ANOVA) and Bonferroni post-processing analysis were used for comparison between-groups. Covariance analysis will be used to adjust the effects of confounding variables. Baseline descriptive data between the intervention and placebo group will be compared using chi-square for categorical variables and *t* tests for continuous variables. The primary outcome of intestinal and nasal microbiota will be performed with the R Programming Language 3.0.1 (NZL).

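### The sizing names a between-factors F test, but its total of 95 is the within-subject (time or time-by-group) result at an epsilon of 0.34, printed as 1.34; the 80% power belongs to time-by-group with two pooled arms

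*Protocol article*

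**What the plan says.** The Sample size section reports a G*Power calculation for an F "test between factors with two groups (intervention and placebo) and three evaluation sessions". The bracket that follows lists four occasions: "before administration, after administration, 12 and 24 weeks after administration". The effect size is a convention, because there was no pilot: "we chose to take the average effect as 0.25". Alpha and power are set by "error probability of 0.05, and a power (1-β error probability) of 0.80". The remaining inputs and the result are given as "We take the Corr among rep measures as 0; the Nonsphericition correction ɛ is 1/(4–1) ≈ 1.34; the resulting total sample size is 95". The section then divides by 4 to reach 24 per group, sets 30 per group after dropout, and arrives at 120 over four arm-by-exposure cells.

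Under Statistical methods, the article plans that "two-way analysis of variance of repeated measurements will be used to explore the impact of time and time-group effects", and separately an ANOVA with Bonferroni adjustment for comparisons between groups.

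**The concern.** The paragraph prints a full set of inputs and a result, so it can be checked, and the parts do not fit together. A between-factors test averages each person's visits and compares the group means. It has no nonsphericity input, so quoting an epsilon suggests that a different procedure was run. The printed epsilon is also impossible.

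This is the only power justification for the group sizes. The two candidate tests answer different questions and respond in opposite ways to the correlation between visits. As the paragraph stands, a reader cannot tell which effect the trial was sized to detect with 80% power.

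**Working it through.** **Inputs from the Sample size section:** f = 0.25, alpha = 0.05, power 0.80, k = 2 groups, m = 4 sessions (3 also tried), rho = 0. Any correlation above 0 below is an assumption, because the article gives none.

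**Formulas** (standard G*Power repeated-measures definitions, noncentral F; assumed, because the article does not state the option used):
- Between factors: lambda = f²·N·m / (1 + (m−1)·rho), with df k−1 and N−k.
- Time-by-group: lambda = f²·N·m·eps / (1−rho), with df (k−1)(m−1)·eps and (N−k)(m−1)·eps. With k = 2, the time test has the same lambda and df.

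**Step 1. Reproduce 95.** Time-by-group, m = 4, rho = 0, eps = 0.34:
- N = 94: lambda = 0.0625 × 94 × 4 × 0.34 = 7.99, power 79.6%.
- N = 95: lambda = 8.075, power 80.1%.

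The smallest N is 95, which is the printed figure.

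**Step 2. The test that is named.** Between factors, rho = 0:
- m = 4: N = 33 gives 79.5%; N = 34 gives lambda = 0.0625 × 34 × 4 = 8.5 and 80.7%. Required total: 34.
- m = 3: N = 44 gives lambda = 8.25 and 80.1%. Required total: 44.
- At N = 95 this test would have 99.8% power (m = 4) or 98.7% (m = 3), not 80%.

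**Step 3. The epsilon.** The text reads "the Nonsphericition correction ɛ is 1/(4–1) ≈ 1.34". But 1/(4–1) = 0.333, and epsilon lies between 1/(m−1) and 1. Required totals for time-by-group at rho = 0:

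| Epsilon | Total |
|---|---|
| 1.34 (as printed, inadmissible) | 37 |
| 0.34 | 95 |
| 1/3 (exact lower bound) | 97 |
| 1 | 45 |

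The exact match at 0.34 suggests that 1.34 is a slip for 0.34, itself a rough rounding of 1/3.

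**Step 4. Correlation and epsilon together.** Zero correlation between every pair of visits, with the equal variances the formula assumes, is a spherical structure. Epsilon is then 1 and the total 45. The lower bound 1/3 cannot hold at the same time. For time-by-group, both choices push the total up.

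**Step 5. Power at the plan's sizes.** Evaluable counts: 4 × 24 = 96 pooled, and 2 × 24 = 48 in one exposure stratum. With no dropout: 4 × 30 = 120 pooled, and 2 × 30 = 60 in one stratum. Time-by-group uses eps = 1/3; both tests use m = 4 and two arms.

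| N | Time-by-group, rho 0 | rho 0.5 | Between, rho 0 | rho 0.3 | rho 0.5 | rho 0.7 |
|---|---|---|---|---|---|---|
| 96 pooled | 80% | 98% | 99.8% | 94% | 87% | 79% |
| 120 pooled | 88% | 99% | >99.9% | 98% | 93% | 87% |
| 48, one stratum | 50% | 79% | 92% | 69% | 57% | 49% |
| 60, one stratum | 59% | 87% | 97% | 79% | 67% | 58% |

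**The case against.** The best defence is that the number is right and only its label is wrong. Statistical methods does plan a time-by-group test. With 95 participants that test has 80.1% power at epsilon 0.34, and with 96 it has 79.9% at epsilon 1/3. Correcting the epsilon moves the total by two participants. The conflict between correlation 0 and a lower-bound epsilon raises the total for this test, so it hides no shortfall. This stands, and it limits the consequence. It does not make the paragraph correct: the named test, the session count, the epsilon and the total cannot all be true together.

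A reader might go further and infer that the 80% belongs to no planned analysis, or that the mislabelling leaves the trial with 49% to 69% power. The documents support neither reading. The first ignores the planned time-by-group test. The second takes between-factors power at 48 participants, a count that arises only from dividing 95 by 4 and then testing one exposure stratum alone. The article does not say that this comparison is the deciding one. It also shows only the test that loses power as correlation rises, whereas time-by-group gains. On the printed inputs, the label by itself over-sizes the named test (34 needed, 95 stated).

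**Conclusion.** The point holds as a mis-stated calculation. The test named in the sizing needs 34 participants (44 with three sessions) on the printed inputs. The 95 comes from the time or time-by-group test with four sessions and epsilon 0.34. The printed epsilon is wrong arithmetically and inadmissible, the session count contradicts its own list, and correlation 0 is incompatible with a lower-bound epsilon, in a conservative direction for time-by-group.

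The 80% can be kept for the time-by-group test with about 96 evaluable participants in two pooled arms. It cannot be kept as the power of a between-factors test. Within one exposure stratum, time-by-group power at epsilon 1/3 and correlation 0 is 50% at 48 and 59% at 60. That shortfall comes from dividing 95 by 4, which is a separate defect, and not from the label or the epsilon.

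These results rest on the standard G*Power formulas, f = 0.25 as stated, and, for every correlation above 0, an assumed value.

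**What to change.** In the Sample size section:
- Name the single test that decides probiotic versus placebo. Time-by-group is the one that fits the printed total. Use the same test under Statistical methods.
- State four sessions.
- Replace 1.34 by an admissible epsilon. If the lower bound is meant, 1/3 gives 97. If a between-factors test is chosen instead, delete epsilon.
- Keep 120 participants. Restate power for the chosen test, pooled over strata and within one stratum, over an assumed correlation range such as 0 to 0.7. For time-by-group at epsilon 1/3 and correlation 0 the figures are 80% at 96 and 88% at 120 pooled, and 50% at 48 and 59% at 60 in one stratum. At an assumed correlation of 0.5 the single-stratum figures are 79% and 87%.
- Attribute any single-stratum shortfall to the division by 4.

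The cost is a recalculation and one rewritten paragraph, with no added participants. The downside is that the stated power may be less favourable, particularly within one stratum or if a between-factors test is kept with a realistic correlation.

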### Outcome measures

The assessment included flora analysis of nasal and intestinal secretions and questionnaires from researchers (all Chinese versions). Assessments will be started before allocation at screening (T0, baseline), 4 weeks after the final treatment (T1, primary endpoint), 12 weeks after the final treatment (T2, secondary endpoint), and 24 weeks after the final treatment (T3, final endpoint). The timeframe of data collection and assessments is shown in Table 1 (the SPIRIT figure).

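### The stated 80% power for f = 0.25 over four sessions, one of them the pre-allocation baseline, should not be read as 80% power for a 0.5 SD arm difference at the primary time point T1

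*Protocol article*

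**What the plan says.** All inputs to the calculation are in the protocol article, Sample size.

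- **Test:** an F "test between factors with two groups (intervention and placebo) and three evaluation sessions". The sessions then listed are "before administration, after administration, 12 and 24 weeks after administration", which makes four.
- **Effect:** "we chose to take the average effect as 0.25". The reason given is the lack of a pilot. No mean, standard deviation or time profile stands behind it.
- **Error rates:** "error probability of 0.05, and a power (1-β error probability) of 0.80", the first figure being alpha.
- **Covariance inputs:** "We take the Corr among rep measures as 0" and "the Nonsphericition correction ɛ is 1/(4–1) ≈ 1.34".
- **Result:** a total of 95, divided by 4 to give 24 per group, raised to 30 for dropout of up to 30%. With four exposure-by-arm groups this gives 120.

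Outcome measures fixes the timing: "Assessments will be started before allocation at screening (T0, baseline"), then "4 weeks after the final treatment (T1, primary endpoint"). Statistical methods plans a repeated-measures two-way ANOVA for time and time-by-group effects. The article does not say whether probiotic and placebo are compared within each exposure stratum or pooled over both.

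**The concern.** In a plain two-group comparison, f = 0.25 is a difference of 2f = 0.5 SD, the conventional medium effect. A reader who sees an average effect of 0.25 with 80% power may take the trial to have 80% power for about 0.5 SD at its primary time point.

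The model that f was entered into is different. It has four sessions, and the first precedes allocation, so randomisation makes the expected arm difference there zero. The whole effect must come from the other three sessions, and how much of it falls at T1 depends on a time profile that the article does not give.

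What is at stake is how a null result is read. It could be taken to exclude a medium effect at T1 when the design has much less than 80% power for one, above all within a single exposure stratum.

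**Working it through.** **Inputs.** From Sample size: f = 0.25, alpha 0.05, power 0.80, k = 2 groups, m = 4 sessions as listed, correlation 0. For the nonsphericity correction, 1/(4−1) = 0.333, although 1.34 is printed. From Outcome measures: expected arm difference zero at T0; T1 primary.

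**Step 1: reproduce 95** (noncentral F).

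- *Between factors (the test named):* λ = N f² m, with df 1 and N − 2. At N = 34, λ = 34 × 0.0625 × 4 = 8.5 and power is 80.7%. This test needs 34, not 95.
- *Time by group:* λ = N f² m ε, with df (m − 1)ε and (N − 2)(m − 1)ε. At ε = 0.34 and N = 95, λ = 95 × 0.0625 × 4 × 0.34 = 8.075, df are 1.02 and 94.86, and power is 80.07%. N = 94 gives 79.65%. This returns exactly 95; at ε = 1/3 it gives 97.
- *Within factor (time):* with two groups the formula is the same, so this also returns 95. It carries no arm difference.

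**Step 2: convert f to an arm difference at T1.** Let d be the arm difference in SD units at T0 to T3, with d = 0 at T0. The between-factors test requires mean(d) = 2f = 0.5. The time-by-group test requires SD(d) over the four sessions (divisor 4) = 2f = 0.5. Scale each profile to meet the requirement and read off T1.

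| Profile (T0, T1, T2, T3) | T1, time by group | T1, between factors |
|---|---|---|
| 0, 1, 1, 1 (sustained) | 1.15 SD | 0.67 SD |
| 0, 1, 0, 0 (T1 only) | 1.15 SD | 2.0 SD |
| 0, 1, 1, 0 | 1.0 SD | 1.0 SD |
| 0, 1, 0.5, 0 | 1.21 SD | 1.33 SD |
| 0, 1, 0.5, 0.25 (fading) | 1.35 SD | 1.14 SD |
| 0, 1, 2, 3 (growing) | 0.45 SD | 0.33 SD |
| 0, 0.5, 1, 1 (growing) | 0.60 SD | 0.40 SD |
| 0, 1, 1.5, 2 (growing) | 0.68 SD | 0.44 SD |

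Example, sustained: the mean is 0.75 and the SD is 0.433, so T1 is 0.5/0.75 = 0.67 or 0.5/0.433 = 1.15.

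**Step 3: what the numbers give at T1.** Two-sample t, two-sided alpha 0.05, noncentrality δ√(n/2), df 2n − 2.

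| Comparison | n per arm | Power for 0.5 SD | Detectable at 80% |
|---|---|---|---|
| One stratum, 30 less 30% | 21 | 35% | 0.89 SD |
| One stratum, calculated size | 24 | 40% | 0.83 SD |
| One stratum, no loss | 30 | 48% | 0.74 SD |
| Pooled, 60 less 30% | 42 | 62% | 0.62 SD |
| Pooled, calculated size | 48 | 68% | 0.58 SD |
| Pooled, no loss | 60 | 78% | 0.52 SD |

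Adjusting for T0 multiplies the detectable difference by √(1 − r²). At an assumed r = 0.5 the factor is 0.87, so 0.83 becomes 0.72 and 0.58 becomes 0.50.

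**Step 4: the division by 4.** The 95 in step 1 counts subjects, each already measured four times. Two arms of 24 are 48 subjects: λ = 48 × 0.0625 × 4 × 0.34 = 4.08, and the time-by-group test has about 50% power for the same f = 0.25.

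**The case against.** - **The article never equates f = 0.25 with 0.5 SD at T1.** True. It is a planning assumption made without a pilot, and entering it is not an arithmetic slip. What stands against the article is narrower: it gives an effect size and a power without saying what they mean at the time point it calls primary.
- **f alone implies no particular T1 difference.** This also stands. A reader might infer that f = 0.25 means 0.7 to 2 SD at T1. Both ends of that range come from the between-factors test, which needs 34 and does not yield 95, and the range assumes no growth after T1. Growing profiles fall below it. Treatment stops after 4 weeks, which makes a persisting or fading effect a natural planning case, but the article does not commit to one. If the time test was run, f describes no arm difference at all.
- **The trial is not sized for a large effect overall.** A reader might infer that it is. The documents do not support this for the pooled comparison: 60 per arm detects 0.52 SD before dropout, and 48 per arm detects 0.50 SD with baseline adjustment at the assumed r = 0.5.
- **The t-test figures depend on n, not on f, and the planned analysis is a repeated-measures ANOVA.** Correct. They show what the chosen size can do at T1. Much of the shortfall comes from dividing 95 by 4, which is a separate error.

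**Conclusion.** The point holds in a limited form. The stated 80% power belongs to an effect spread over four sessions, one of which cannot carry a treatment effect in expectation. It is not 80% power for 0.5 SD at T1. Within one exposure stratum, power for 0.5 SD is 35% to 48%, and only this comparison needs a difference near the conventional large value of 0.8 SD. Pooled over strata, power is 62% to 78%, with a detectable difference between medium and large.

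The time-by-group conversion of 1.0 to 1.35 SD rests on correlation 0, four sessions and an effect that does not grow after T1. The power figures rest on an unadjusted comparison at T1 alone of a roughly normal outcome. Chance imbalance at T0 remains possible; only its expectation is zero.

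**What to change.** In Sample size, beside or in place of the average effect of 0.25, state the T1 arm difference detectable with 80% power:

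- within one stratum: 0.89 SD at 21 per arm, 0.83 SD at 24, 0.74 SD at 30;
- pooled: 0.62 SD at 42 per arm, 0.58 SD at 48, 0.52 SD at 60.

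Use the enrolled 30 per group and the 21 left after 30% dropout as the bounds, and do not present 24 as what the enrolled size detects. Give the power for 0.5 SD alongside, and say whether the comparison is within stratum or pooled. Label any baseline-adjusted figure with its assumed T0–T1 correlation. Name the F test and the ε that produced 95, and correct the division by 4 as a separate item.

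Restating the detectable difference costs wording only and adds no participants; the stated sensitivity becomes less favourable.

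### The sample-size calculation sets the within-person correlation to 0 without justification, which overstates power for the between-factors test it names

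*Protocol article*

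**What the plan says.** All inputs are in the Sample size section of the protocol article.

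- **Test:** a G*Power F "test between factors with two groups (intervention and placebo) and three evaluation sessions (before administration, after administration, 12 and 24 weeks after administration"). The text says three sessions but lists four time points.
- **Effect size, alpha and power:** "we chose to take the average effect as 0.25", an alpha "error probability of 0.05", and "a power (1-β error probability) of 0.80".
- **Correlation:** "We take the Corr among rep measures as 0". The absence of a pilot is mentioned, but as the reason for the effect size.
- **Nonsphericity:** "the Nonsphericition correction ɛ is 1/(4–1) ≈ 1.34".
- **Result:** "the resulting total sample size is 95, because it has to be repeated 4 times", which leads to 24 per group. This is raised to 30 for dropout and then doubled to cover a high- and a low-exposure pair, giving 120.

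The Background says the nasal mucosa is not readily disturbed by outside influences, "so the resident microbiota in the nasal cavity is also one of the typical characteristics of our body". It makes no such statement about the gut, and it adds that fine particles can alter both. Nasal and gut diversity are both primary outcomes. The Statistical methods section plans a repeated-measures analysis of time and time-by-group effects, and also an ANOVA for comparisons between groups.

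**The concern.** A correlation of 0 treats four visits by one participant as if they came from four unrelated people. Samples from one person normally resemble each other more than samples from different people. The Background relies on that idea when it justifies the nasal outcome.

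The direction of the error depends on the test. A between-factors test compares each group's average over visits, so positive correlation makes the repeat visits partly redundant and lowers power. A time-by-group test works on changes within a person, so positive correlation removes noise and raises power. The section names the first kind of test, for which zero is the most favourable value in the non-negative range. If that test is primary, the stated 80% may not be met.

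**Working it through.** **Inputs.** From the Sample size section: f = 0.25, alpha = 0.05, k = 2 groups, m = 4 visits (the number listed), 24 or 30 per group. The document gives no non-zero correlation, so rho = 0.3, 0.5 and 0.7 is an assumed range.

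**Formulas** (repeated-measures ANOVA, noncentral F):

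- Between factors: lambda = f² · N · m / (1 + (m − 1)rho), with df = k − 1 and N − k.
- Time-by-group: lambda = f² · N · m · eps / (1 − rho), with df = (m − 1)(k − 1)eps and (N − k)(m − 1)eps.

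**Step 1: reproduce 95.** The printed nonsphericity value cannot be right, since 1/3 is about 0.33 and eps cannot exceed 1. With eps = 0.34, rho = 0 and N = 95, the time-by-group test has lambda = 0.0625 × 95 × 4 × 0.34 = 8.075 on 1.02 and 94.86 df. Power is 0.801, and 95 is the smallest N that reaches 80%. With eps exactly 1/3 the answer is 97. The between-factors test at rho = 0 needs only N = 34 (lambda = 0.0625 × 34 × 4 = 8.5). So 95 belongs to the time-by-group test, although the text names between factors.

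**Step 2: the named test, one exposure stratum.** With 2 × 24 = 48, lambda = 0.0625 × 48 × 4 / (1 + 3rho) = 12 / (1 + 3rho). With 2 × 30 = 60 and no dropout, it is 15 / (1 + 3rho).

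| rho | lambda, N = 48 | power, N = 48 | lambda, N = 60 | power, N = 60 |
|---|---|---|---|---|
| 0 | 12.00 | 92% | 15.00 | 97% |
| 0.3 | 6.32 | 69% | 7.89 | 79% |
| 0.5 | 4.80 | 57% | 6.00 | 67% |
| 0.7 | 3.87 | 49% | 4.84 | 58% |

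Power falls below 80% once rho exceeds about 0.16 at N = 48, and about 0.28 at N = 60. With the protocol's own 30% loss from 60 (42 completers) the threshold is about 0.09. The total N needed for 80% power is 34, 62, 81 and 100 at rho = 0, 0.3, 0.5 and 0.7.

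**Step 3: the time-by-group test (eps = 0.34).**

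| rho | power, N = 95 | power, N = 48 | N for 80% |
|---|---|---|---|
| 0 | 80% | 50% | 95 |
| 0.3 | 92% | 65% | 67 |
| 0.5 | 98% | 80% | 49 |
| 0.7 | 99.9% | 95% | 30 |

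Here zero is the conservative choice. The 50% at N = 48 has another cause: 95 is already a number of participants, and it was divided by the number of visits.

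**Step 4: strata pooled, 4 × 24 = 96, two arms compared.** The between-factors test has power 99.8%, 94%, 87% and 79% at rho = 0, 0.3, 0.5 and 0.7, and stays above 80% up to rho of about 0.67. The time-by-group test has 80.5% at rho = 0 and more at any positive rho.

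**The case against.** The strongest reply is that the test which yields 95 is the time-by-group test. It also matches the time-by-group effect in the Statistical methods section, and for it rho = 0 does no harm: 80% at N = 95 is a floor. That stands. A reader might infer that the zero correlation undermines the stated power whichever test is meant. The documents do not support this. For the time-by-group test the shortfall at 24 per group comes wholly from the division by 4.

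A reader might also say that the stated 80% shifts by some 35 to 45 points once rho is realistic. That is not what the figures show. At N = 48 the starting points at rho = 0 are 92% and 50%, neither of them 80%, and in the second case power improves.

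The reply can add that the article does not fix whether the strata are pooled, and that pooling largely protects the between-factors test. That also stands as a qualification. However, the section sizes one pair of arms at 24 each and only afterwards duplicates the pair for the two exposure levels, and randomization is done within each exposure group. One stratum is therefore the natural reading of the section's own arithmetic.

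Finally, the stability rationale concerns the nose only and gives no value for rho. That is correct. It supports a positive correlation for the nasal outcome, not a particular figure, and it says nothing of the kind about the gut.

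**Conclusion.** The point holds in a limited form. Zero correlation is unjustified, implausible for repeat samples from one person, and at odds with the Background for the nasal primary outcome. For the between-factors test that the section names, at its own two groups of 24, it overstates power: 92% at rho = 0 against 69%, 57% and 49% at rho = 0.3, 0.5 and 0.7. The 80% is lost above rho of about 0.16. With 30 per group and no dropout the figures are 79%, 67% and 58%.

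This rests on the between-factors test being primary, on analysis within one exposure stratum, on four visits, and on an assumed range for rho. If the time-by-group test is primary, rho = 0 is conservative. If the strata are pooled, the between-factors test is short of 80% only above rho of about 0.67. The point should be fixed; because it depends on those choices, it is not among the changes that must be made.

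**What to change.** In the Sample size section:

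1. Name the one test that is primary, and say whether it is run within each exposure stratum or with the strata pooled.
2. Replace the zero correlation with a stated positive range, for example 0.3 to 0.7, labelled as assumed.
3. Rerun the calculation for that test with a valid nonsphericity value where one applies. Treat the G*Power total as participants, without dividing by the number of visits.
4. Restate the power at 24 and at 30 per group over the range. Enrolment stays at 120.

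The cost is one rerun and a rewritten paragraph. The single 80% becomes a range, which will be less favourable if the between-factors test within a stratum is kept.
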